### Criteria for discontinuing or modifying allocated interventions {11b}

If clinical deterioration, an adverse event (AE) or a serious adverse event (SAE) is detected throughout the course of the trial by an outcome assessor or facilitator, it will be promptly reported to the research team, trial sponsor, ethics committees and Data Safety and Management Board (DSMB), see Sect. 22 for further details. Where an AE or SAE occurs, participants will be referred to specialist support if deemed necessary by the research director and research team using previously developed remote referral pathways. Clinical deterioration includes instances where a participant is intoxicated during multiple sessions, reports suicidal ideation, or homicidal ideation. Participants who report suicidal ideation will only be referred to specialist services or withdrawn from the trial if they are at imminent risk of suicide, which involves having a plan in place. Participants referred to specialist support during baseline outcome assessment or the CHANGE intervention sessions will be withdrawn from the trial but may continue to receive the remaining CHANGE sessions. If participants are referred to specialist support at the 3-month outcome assessment, they will not be withdrawn from the trial. All facilitators and outcome assessors have received training in safety protocols for remote service delivery and to ensure adherence to best practice.

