A critical incident register will be maintained during the study to record specific SAEs and AEs. An overview of the types of SAEs and AES can be found in Table 5. SAEs and AEs that are detected during any of the outcome assessments or intervention sessions will be disclosed immediately to the local research director and site PI who will become unmasked. For each individual event, a report will be written. Based on the type of event, the participant will be asked to give consent for further evaluation, assessment, and/or follow-up by a designated health professional (see Table 6). If the participant experiencing an AE or SAE was in the intervention arm of the trial, and once they are referred to further care their data will be excluded from the analysis. Nonetheless, if they are able to, they can receive further CHANGE sessions. The exception to this is referrals for intimate partner violence, whereby participants will be encouraged to access protection services, but will not be excluded from the analysis.

**Table 5 Tab5:** Expected and unexpected SAE and AEs (adapted from Van Der Boor et al., 2024 [23])

	Expected	Unexpected
SAE	Victimization (violence against the trial participant or nuclear family)	Death of the trial participant due to suicide
	IPV (violence against family members by participant, or violence against participant by family member)	Death of the trial participant due to other causes
	Suicide attempt	Hospital admission of trial participant due to a psychiatric problem
	Homicidal ideation	Planning and/or going through with the homicidal ideation
	Stigmatisation	Hospital admission of trial participant due to other causes (i.e. serious medical emergency)
	Serious lack of food / Critically unsatisfied basic needs	
AE	Clinical deterioration of the participant	
	Emotional distress caused by a trial procedure (either by the outcome assessment or the intervention delivery)

**Table 6 Tab6:** SAE referral according to intervention arm

SAE	Reported at outcome evaluation in both arms, referral to:	Reported by facilitator in the intervention arm only, referral to:
Hospital admission of participant due to serious medical emergency^a^	General physician (GP), family doctor	GP, family doctor
Hospital admission of participant due to a psychiatric problem	Independent psychiatrist, Psychiatrist in the hospital	Independent psychiatrist, Psychiatrist in the hospital

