Victimisation (violence against the participant)	Independent psychologist, social worker, humanitarian agency representative	Intervention supervisor
Severe IPV perpetrated by participant (violence against family members by participant) that includes a risk of severe injury and/or death	Independent psychologist, social worker, humanitarian agency representative	Intervention supervisor
Suicide attempt	Independent psychiatrist, Psychiatrist in the hospital	Independent psychiatrist, Psychiatrist in the hospital
Homicidal ideation	Independent psychiatrist, Psychiatrist in the hospital	Independent psychiatrist, Psychiatrist in the hospital
Stigmatization^a^	Intervention supervisor	Intervention supervisor
Death of the trial participant	N/A	N/A
Any violence toward others	Independent psychiatrist, social worker, humanitarian agency representative	Independent psychiatrist,
Serious lack of food/ Critically unsatisfied basic needs	GP, primary health care worker (nurse/ midwife)	GP
**AE**		
Clinical deterioration of trial participant, including a high risk of a suicide attempt	Independent psychiatrist, Psychiatrist in the hospital	Independent psychiatrist, Psychiatrist in the hospital
Emotional distress caused by a trial procedure (either by the outcome assessments or the intervention delivery)	Independent psychologist, Psychiatrist in the hospital	Independent psychologist, Psychiatrist in the hospital

^a^Prior to referral to the nominated healthcare professional, these SAEs will have an independent clinician review the SAE narrative to determine if this is indeed a SAE

During the 3-month follow-up assessment, all participants will be asked to respond to the safety questions (related to suicide and homicidal ideation) again. In the case of an SAE detection, an independent psychiatrist will assess the participant, and the SAE report will be completed. Participants with safety issues identified during the follow-up will not be excluded from the trial. These questions aim to identify any problems and provide timely referral pathways.

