When an SAE is related to stigma, a report will be written as described above, and an evaluation will be conducted by an independent healthcare provider to ensure quality and correct identification of these types of SAEs. Irrelevant of the cause, for events determined by the independent clinician to be SAEs, the person who became aware of the event (outcome assessor or facilitator) will then forward the SAE for further referral to the appropriate professional. The time from initial detection of a potential SAE by the research team (e.g. outcome assessors and facilitators), to the responsible team member (outcome assessor or facilitator) sending the SAE/AE report to the nominated health professional is two working days. Following these 2 days, if it classifies as an SAE, the responsible team member will inform the research director, who will prepare and submit the report to the site PI, who will send it to overall PI, DSMB and respective ethics committees within 5 working days of detection. All SAEs and AEs will be followed up until they have abated, or until a stable situation has been reached. AEs will not be reported to the DSMB but will be included in the annual ethics report.

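### Two sections give opposite rules on whether AEs reach the DSMB, and event counts by arm are confounded by more detection contacts in CHANGE

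*Protocol article*

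**What the plan says.** Section {11b} of the protocol article (discontinuing or modifying interventions) begins "If clinical deterioration, an adverse event (AE) or a serious adverse event (SAE) is detected throughout the course of the trial" and continues "it will be promptly reported to the research team, trial sponsor, ethics committees and Data Safety and Management Board (DSMB". It refers the reader to section 22 for details. It also defines clinical deterioration to include repeated intoxication at sessions, suicidal ideation and homicidal ideation.

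Section {22} (adverse event reporting) sets a different route. A report on an event classified as an SAE goes to the site PI, "who will send it to overall PI, DSMB and respective ethics committees within 5 working days of detection". For the rest, "AEs will not be reported to the DSMB but will be included in the annual ethics report".

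Table 5 lists two AE types: clinical deterioration, and distress brought on by a trial procedure. Table 6 describes the first as "Clinical deterioration of trial participant, including a high risk of a suicide attempt". Table 5 places homicidal ideation and suicide attempt among the expected SAEs.

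On detection, {22} refers to events found at outcome assessments or intervention sessions, and Table 6 has a separate column for facilitator reports, which exist in the intervention arm alone. At 3 months, "all participants will be asked to respond to the safety questions (related to suicide and homicidal ideation) again". Section {21a} makes the DSMB the body that judges whether a safety problem exists and the only committee with unmasked data during the trial.

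**The concern.** Staff who find an AE have two written instructions, and following one breaks the other. The ethics route conflicts as well: prompt notification in {11b}, an annual report in {22}. The AE category is not limited to minor complaints. It holds high risk of a suicide attempt, suicidal ideation and distress caused by the trial itself, which are the harms most relevant to a psychological intervention for distressed men. If {22} is followed, these events are outside the reporting line to the body charged with judging safety.

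The second part concerns how counts by arm would be read. CHANGE participants are seen weekly by a facilitator who can report events; EUC participants are not. An excess of events in CHANGE could come from closer observation alone. Conversely, similar counts in the two arms could hide more undetected events in EUC.

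**Working it through.** The plan states no figure to reproduce. The check sets the sections side by side and counts contacts.

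**Step 1: reporting route by event.**

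| Event | Under {11b} | Under {22} and Table 5 |
|---|---|---|
| Clinical deterioration, including high suicide risk | Prompt, DSMB and ethics committees | AE: not to the DSMB; annual ethics report |
| Distress from a trial procedure | As an AE: prompt, DSMB and ethics committees | AE: not to the DSMB; annual ethics report |
| Homicidal ideation | Named as clinical deterioration: prompt, DSMB and ethics committees | As clinical deterioration, an AE: not to the DSMB. As a Table 5 SAE: DSMB within 5 working days |
| Other SAEs | Prompt, DSMB and ethics committees | DSMB and ethics committees within 5 working days |

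The first two rows, which are both of the listed AE types (2 of 2), conflict outright. The third depends on which classification is used. Only the last is consistent. The pointer in {11b} to section 22 does not settle the matter, because {11b} itself names the DSMB as a recipient.

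**Step 2: scheduled detection contacts after randomisation.** Inputs: six weekly sessions with an optional booster ({11a}); assessments at baseline and 3 months, so one after randomisation ({12}).

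- CHANGE: 6 + 1 = 7, or 8 with the booster, at full attendance.
- EUC: 1.

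The EUC consultation is given to both arms around randomisation, and EUC specialists are not named as detectors of events, so it does not restore balance. The check-ins in {22} apply only to cases already known to be high-risk.

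**Step 3: what the common 3-month interview covers.** The safety questions appear in {10}. Three are listed, on suicide and harm to others, and two of the three refer to the last month. If the same wording is used again, those two cover about 1/3 of a 3-month follow-up. The violence measure in Table 3 asks both arms about perpetration over the last 3 months, so that event type is covered evenly. The article describes no common question, with recall since randomisation, for the other Table 5 events, such as victimisation, stigmatisation or hospital admission.

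**Step 4: illustration of size.** Let p be the probability that one contact detects an event that stays detectable throughout, equal and independent across contacts. The documents do not give p; the values are assumptions. Probability of detection = 1 − (1 − p)^m, with m = 7 for CHANGE and m = 1 for EUC. There is no true difference between arms.

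| p | CHANGE | EUC | Apparent ratio |
|---|---|---|---|
| 0.1 | 52% | 10% | 5.2 |
| 0.3 | 92% | 30% | 3.1 |
| 0.5 | 99% | 50% | 2.0 |
| 0.9 | about 100% | 90% | 1.1 |

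Example: p = 0.1 gives 1 − 0.9^7 = 0.522, and 0.522/0.1 = 5.2.

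**The case against.** The conflict between {11b} and {22} has no good defence, but several stronger readings go too far.

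- A reader might infer that events are actively sought every week in CHANGE. The text says only that they are detected at sessions or reported by facilitators; no weekly safety questioning is described. Sessions are offered, so 7 contacts is a maximum, and they cover about 6 of roughly 13 weeks.
- A reader might infer that nothing from the first two months is elicited in EUC. Partner violence by the participant is asked over 3 months in both arms, and only two of the three safety questions carry a one-month limit.
- A reader might infer that the DSMB never sees AEs, or that neither harm nor reassurance can be drawn from its data. It has access to unmasked data, AEs enter the critical incident register, its charter is not shown, and suicide attempts are SAEs that reach it under {22}. Deaths and hospital admissions depend less on session contact than stigma or unmet need do.
- A reader might see further contradictions in timing and masking. Section {22} has events "will be disclosed immediately to the local research director and site PI who will become unmasked" and later says "Following these 2 days, if it classifies as an SAE, the responsible team member will inform the research director". These can be read as an immediate alert followed by a formal SAE report. Unmasking of the site PI reads as a stated exception to the general rule in {17a}.

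It can also be said that the article announces no between-arm comparison of harms, that elicitation forms belong in the full protocol, and that a DSMB table of AEs takes one side of the conflict. The first two have some force and make unequal detection the secondary part of this point. On the third, a periodic summary by arm is distinct from prompt reporting of single events, and that choice remains with the sponsor.

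**Conclusion.** The contradiction stands on the text and needs no assumption: {11b} and {22} cannot both be followed for AEs, for either of the two AE types, and the route for homicidal ideation is unclear. It should be corrected while the trial is running.

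Unequal detection also stands, as a limit on interpretation: up to 7 scheduled contacts against 1. How far it distorts counts is unknown. The illustrated ratios of 1.1 to 5.2 rest on an assumed detection probability, full attendance and persistent events. The supported conclusion is that event counts by arm are confounded by intensity of observation, most for events that come to light only through contact. The documents do not show that the counts are uninformative.

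**What to change.** 1. Reconcile {11b} and {22} so that one reporting route applies to AEs, for both the DSMB and the ethics committees. Reconcile the classification of homicidal ideation between {11b} and Table 5. Which reporting and classification rule is right is for the sponsor and its committees.
2. Include AEs alongside SAEs, by arm, in the table for the existing twice-yearly DSMB meetings. The {22} sentence excluding AEs would need rewording to allow this.
3. In the 3-month interview, ask both arms the same Table 5 events with recall since randomisation. Use the answers for any between-arm comparison of harms, and tabulate facilitator-detected events separately. Placing the block late in the interview protects the primary outcome if an answer unmasks the assessor.

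The cost is protocol wording with the ethics approvals that {25} requires, one DSMB table, and a few minutes added to an interview of about 2 hours. Recruitment began in September 2024 and is expected to finish in 2026, so the new questions would cover only participants interviewed after the change. The harms comparison based on them should be limited to that group in both arms.

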### Frequency and plans for auditing trial conduct {23}

A bi-annual meeting will be held with the TSC to review the progress and ensure that the trial is conducted in accordance with the protocol and relevant regulations. The DSMB will similarly meet biannually with the aim of monitoring the RCT data. The DSMB is the only body involved in CHANGE that has access to the unmasked data during the trial. Furthermore, a yearly report will be submitted to the Ethics Committee at the London School of Hygiene and Tropical Medicine (LSHTM) to detail progress. These three bodies are independent from investigators and the sponsor, and will be overseeing both the CHANGE trial in Ukraine and Uganda.

### Plans for communicating important protocol amendments to relevant parties (e.g. trial participants, ethical committees) {25}

Protocol amendments will only be implemented following approval by the London School of Hygiene and Tropical Medicine ethics committee and local NaUKMA ethical approval.

### Dissemination plans {31a}

An ISRCTN public trial registration has been completed (ISRCTN14881856). The findings of the effectiveness and cost-effectiveness trial, and process evaluation in Ukraine will be submitted for peer-reviewed publication in international journals. The results will also be shared with key stakeholders (e.g. Ministry of Health, heath clusters, non-governmental organisations, community organisations) through individual country reports and briefs in English, Ukrainian and Russian spoken in Ukraine. Other outputs will include presentations at international conferences and workshops, and findings will be circulated amongst the humanitarian community on platform used by humanitarian workers (e.g., MHPSS.net and MHIN). The next steps in the research project will involve examining the scalability of the CHANGE intervention through the health system and other humanitarian sectors in Ukraine.

## Discussion

The current paper details a trial assessing the effectiveness and cost-effectiveness of the CHANGE intervention in reducing alcohol misuse and psychological distress in war-affected men in Ukraine. Following the current research, an open-access manual developed for implementing the CHANGE intervention in Uganda and Ukraine will be made publicly available. Should the CHANGE intervention prove effective, it can be adopted in other war-affected regions to further evaluate its effectiveness and cost-effectiveness in diverse contexts.

Additionally, the process evaluation of the CHANGE intervention’s implementation will provide valuable insights into the delivery of public health interventions amid ongoing conflict, such as the one in Ukraine. This evaluation will examine the impact on intervention delivery, the implementers, and the overall outcomes of the intervention and will facilitate important reflections around the use of implementation research and frameworks in unstable settings.

### Trial status

The current paper is based on the 4th version of the study protocol (date: 06/02/2025). The first recruitment took place on September 4th, 2024 and we expect the final recruitment to be completed in 2026.

## Data Availability

The datasets generated during and/or analysed during the current study will not be made publicly available as participants have not consented to this.

## Abbreviations

AE: Adverse events
AUDs: Alcohol use disorders
AUDIT: Alcohol Use Disorder Identification Test
CAP: Counselling for alcohol problems
CETA: Common Elements Treatment Approach
CONSORT: Consolidated Standards of Reporting Trials
DALY: Disability-adjusted life years
DSMB: Data Safety and Management Board
ENACT: Enhancing Assessment of Common Therapeutic factors tool
EUC: Enhanced usual care
EQUIP: Ensuring Quality in Psychological Support platform
EQ-5D-5L: EuroQol 5 Dimensions, 5 Levels
GDPR: General Data Protection Regulations
GP: General physician
IDPs: Internally displaced persons
ISRCTN: International Standard Randomised Controlled Trial Number
ITT: Intention to treat
K10: Kessler Psychological Distress Scale
LSHTM: London School of Hygiene and Tropical Medicine
MHAI: Mental Health Assessment Inventory
mhGAP: Mental Health Gap Action Programme
NIHR: National Institute for Health Research
NaUKMA: National University of Kyiv-Mohyla Academy
OECD: Organisation for Economic Co-operation and Development
ODA: Official Development Assistance
ODK: Open Data Kit
PDA: Percentage of days abstinent
PIs: Principal investigators
PM +: Problem Management Plus
PTSD: Post-traumatic stress disorder
QALY: Quality-adjusted life years
RCT: Randomised controlled trial
SAE: Serious adverse event
TMC: Trial Management Committee
TSC: Trial Steering Committee
WHO: World Health Organisation
